# Background

The use of alcohol in South Africa is among one of the highest of Africa^1^, with an adult per capita consumption of 9.5 liters of pure alcohol per year (2003-2005 period)^2^. However, if only taking into consideration the people that drink alcohol, the total adult per capita consumption is 34.91 liters of pure alcohol per year (men 39.64, women 23.84 liters)^2^. Since South Africa also has one of the highest prevalence of HIV in the world with a current prevalence estimated to be 17.8% [17.2%-18.3%]^3^ it is possible that a considerable number of HIV positive people consume alcohol.

Studies from Southern and Eastern Africa showed that in adults who have a history of alcohol consumption or frequently use alcohol, the HIV prevalence is considerably higher than in adults that do not use alcohol.^4,5,6,7^ Percentages range from 10% in individuals who ever drank alcohol compared to 5% of individuals who never drank alcohol^8^, to 58.6% in women drinking alcohol in a township in South Africa compared to 34.7% of women who never drink alcohol^9^. Individuals that drink alcohol have an increased risk of HIV infection compared to adults with no history of alcohol consumption (odds up to 2.5 times higher)^10^. A systematic review and meta-analysis by Fisher et al. confirmed the strong association between alcoholuse and HIV infection^11^.

It has been shown that alcohol use in HIV positive patients has numerous negative effects. An association has been shown between alcohol use and high-risk sexual behavior and risk of HIV^12,13^. Participation in pretest counseling among women attending PMTCT services was significantly higher in women with a low alcohol score compared to women with a high alcohol score (Odds ratio (OR)=0.71). Also posttest counseling participation was higher in women with low alcohol score (OR=0.65)^14^. Alcohol use was a predictor of failure to return for HIV test results among pregnant women in Tanzania. In women using alcohol daily the adjusted OR (aOR) was 1.24 (95% CI: 0.41-3.77) and 1.55 (95% CI: 1.06-2.25) for women drinking alcohol occasionally^15^. Alcohol use was associated withlate presentation to HIV care (OR 3.55, 95% CI: 1.63-7.71)^16^.

Alcohol use in HIV patients also has negative effects on adherence. In a study from Botswana alcohol use influenced 37.0% (n=148) patients to miss ART doses^17^. It was also associated with poor adherence in a study from India (adjusted OR 5.68)^18^, West-Africa(OR 1.4, CI 1.1-2.0)^19^, the Democratic Republic of Congo (17 out of 44 patients (39%) who reported to have missed ART>2 consecutive days during the last month report to drink at least more than 1 alcoholic drink a day compared with 491 of 1909 (26%) who did not report missed antiretroviral doses > 2 consecutive days (OR=1.82, 95% CI: 0.94 to 3.49)^20^ and in a study looking at adherence in 5 African countries^21^.

HIV disease progression is accelerated by alcohol use as shown in different studiesin which frequent alcohol users (defined by 2 or more drinks daily) were 2.91 times (95% CI: 1.23-6.85) more likely to present a decline of CD4 to ≤200 cells/µL, independent of baseline CD4 cell count and HIV viral load, ART use over time, time since HIV diagnosis and age and gender. Frequent alcohol users who were not on ART also had an increased risk for CD4 cell decline to ≤200 cells/µL (HR=7.76, 95% CI 1.2-49.2)^22^. A study by Samet et al. showed that heavy alcohol consumption was associated with a lower CD4 cell count (adjusted mean decrease of 48.6 cells/µL compared with abstinence; p=0.03) in patients who were not on ART. In patients on ART there was no association found between heavy alcohol consumption and lower CD4 cell count.^23^

Conigliaro and colleagues showed that patients with alcohol diagnoses more often had elevated alanine transaminase or aspartate transaminase levels (p≤0.02) (which could add to the risk of toxicity), anemia (p<0.001) and elevated mean corpuscular volume (P<0.001). Also hazardous and/or binge drinkers more often had a detectable viral load (P<0.001)^24^. Finally, a method to quantify the fraction of HIV/AIDS deaths attributable to alcohol consumption from non-adherence to ART shows that the effects of alcohol on HIV/AIDS in the African Global Burden of Disease regions range from 0.03% to 0.34% for men and from 0% to 0.17% for women, depending on region and age category. The detrimental effect of alcohol consumption was statistically significant in every region and age category except for the North Africa/Middle East region.^25^

Very few reports from resource limited settings are published on interventions to reduce alcohol use in HIV positive patients. One study describes an intervention based on culturally adapting 6 session (over a 3 month period) cognitive-behavioral therapy (CBT) to reduce alcohol use among HIV-infected outpatients in Western Kenya, whereby percent days abstinent from alcohol (PDA) before session 1 was 52-100% (women) and 21-36% (men). By session 6 this was 96-100% for women and 89-100% for men. PDA effect sizes (Cohen’s d) between first and last CBT session were 2.32 (women) and 2.64 (men). Participants were also satisfied with the treatment^26^. Another intervention set in Zimbabwe aimed to reduce the sexual risk behavior associated with men’s alcohol consumption and was evaluated in a randomized controlled trial implemented in 24 beerhalls. It was a male-focused, peer-based intervention promoting the idea that men can assist their friends in avoiding high-risk sexual encounters associated with alcohol drinking. The levels of risk behavior declined in both the control as intervention arm. The intervention did not add an impact on the alcohol dependency (the primary outcome measure; episodes of unprotected sex with non-wife partners in the preceding 6 months; also did not differ in the two groups)

# Problem statement

Alcohol use and HIV are closely related and the consequences for individuals with HIV infection who use alcohol are negative in a broad spectrum, including increased sexual risk behavior and psychosocial problems (depression). Since the combined occurrence of epidemics of HIV and alcohol use has been found to be a major problem in South Africa there is a need for action to reduce alcohol use among HIV positive patients. A randomized controlled trial is proposed aimed at evaluating Screening and Brief Intervention (SBI) for Alcohol problems among HIV out-patients in the clinics under the [name] Hospital, Ga-Rankuwa, South Africa.

# Purpose/Aim/Objectives

#### Aim

To study the efficacy of a Screening and Brief Intervention (SBI) for alcohol problems-project in HIV-positive out patients.

#### Objectives:

- - 1. To measure the prevalence of alcohol consumption among HIV positive hospital outpatients;
    2. To describe drinking patterns, health status, quality of life and sexual behavior among HIV positive out-patients, and identify medium risk drinkers needing intervention;
    3. To compare level of alcohol consumption, health status, quality of life, level of adherence to ART and sexual behavior among medium risk drinkers within the previously identified group between pre intervention, 3 months and 12 months after intervention;
    4. To compare **levels of** (a) alcohol consumption, (b) adherence level to ART, (c) quality of life, (d) health status and (e) number of patients with virological and immunological failure, between intervention and control group at 3 and 12 months;
    5. To compare **changes in** (a) alcohol consumption, (b) adherence level to ART, (c) quality of life, (d) health status and (e) number of patients with virological and immunological failure, between intervention and control group at 3 and 12 months.

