#### Sample size calculation

The sample size was calculated using Open Epi (available on www.openepi.com), for a two arm randomized controlled trial. With 80% power, a significance level of 5%, two sided-tests, assuming that adherence levels to ART overall are 90% in Africa. The adherence level of moderate alcohol users compared to abstainers and minimal alcoholusers shows an odds ratio of 0.480^27^. The minimum sample size for each group is 251 patients. To accommodate a drop-out rate of 10% overall, the sample size for each group will be 276, making a total of 552 patients.

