###### Control arm:

Participants randomized to this group will not receive feedback on the initial alcohol screening. They will be provided with a health education leaflet on responsible drinking (Annex 6), and they will only receive the brief intervention after the 12 month follow-up if the intervention has proved to be efficacious.

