# Data Analysis

*Definition of virological failure:*

We follow the definition used in the national guidelines in which virological failure is defined as a repeat VL ≥ 1000 copies/ml after intense adherence assessment^38^.

*Definition of immunological failure:*

Immunological failure is defined according to the WHO definition. Failure is defined as a fall of CD4 count to pretherapy baseline (or below), *or* a 50% fall from the on-treatment peak value (if known) *or* a persistent CD4 levels below 100 cells/mm^3^.^39^

Means, standard deviations, and percentages will be used for descriptive statistics. T-test for continuous data and chi-square for categorical data will be used to examine differences between groups. Generalized Linear Model Repeated Measures 2 x 3 Analysis of Variance (ANOVA) will be used for comparing observations (alcohol use score) across the three contact periods to demonstrate a treatment intervention x time interaction.Observations with a single follow-up point missing (at either 3 and 12 months) will be imputed with the available follow-up. Data for participants who are lost to follow-up at 3 and 12 months will be imputed using baseline values. SPSS for Windows version 18.0 (SPSS, Inc., Chicago, IL) will be used for calculations.

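### No primary outcome or efficacy criterion is fixed: the trial is sized on ART adherence, aimed at and modelled on alcohol, and lists the same five outcomes for comparison both as levels and as changes

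*Protocol*

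**What the plan says.** - **Objectives 4 and 5.** Alcohol consumption, ART adherence, quality of life, health status, and virological and immunological failure are compared "between intervention and control group at 3 and 12 months". Objective 4 does this for levels and objective 5 for changes. Nothing ranks the five.
- **Aim and Hypotheses.** The aim is efficacy of screening and brief intervention for alcohol problems. The first hypothesis is a larger fall in drinking in the intervention arm. The third covers all five outcomes together.
- **Sample size calculation.** The basis is adherence: "With 80% power, a significance level of 5%, two sided-tests", "assuming that adherence levels to ART overall are 90% in Africa", and moderate drinking that "shows an odds ratio of 0.480" against little or no drinking. The result is: "The minimum sample size for each group is 251 patients".
- **Data Analysis.** t-tests and chi-square tests are planned for differences between groups. The only model tied to an outcome is a 2 x 3 repeated-measures ANOVA for "comparing observations (alcohol use score) across the three contact periods", aimed at a treatment-by-time interaction.
- **Control arm.** Controls receive the brief intervention after the 12-month visit only "if the intervention has proved to be efficacious".
- **Ethical issues, Adequacy of Protection against Risks.** This section says, without any condition, that every participant will receive the intervention.

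**The concern.** A protocol may leave a multiplicity procedure to an analysis plan. Here the difficulty is that sections which should agree on what the trial is about do not. One outcome sets the number of patients, another is the subject of the aim and the model, and the objectives put both in an unranked list of five.

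Two consequences follow. First, the meaning of a positive trial could be settled after the data are seen, and the false-positive rate depends on that choice. Second, objectives 4 and 5 ask for two answers about the same treatment effect. A comparison of 12-month levels and a comparison of changes from baseline estimate the same quantity under randomisation, but they use baseline differently. One can be significant and the other not, and nothing says which is then reported as the result. A decision about the control arm also hangs on a verdict that has no definition.

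**Working it through.** **1. Reproduce the stated sample size.** The inputs are from Sample size calculation: p1 = 0.90, odds ratio 0.48, two-sided 5%, 80% power.
- Odds in the second group: 0.48 x 0.90/0.10 = 4.32, so p2 = 4.32/5.32 = 0.812.
- Mean proportion 0.856; difference 0.088.
- n per group = (1.96 + 0.84)² x 2 x 0.856 x 0.144 / 0.088² = 250.02 with unrounded inputs, rounded up to 251. This matches the protocol.
- 251 x 1.1 = 276.1, stated as 276.

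The calculation therefore belongs to a comparison of adherence proportions. It says nothing about the alcohol score.

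**2. Count the comparisons.** 5 outcomes x 2 forms (level, change) x 2 visits = 20. Counting the two failure types apart gives 6 x 2 x 2 = 24.

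**3. Error rate if any of them could count, all tests independent.**

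| Tests | Significant in either direction, 1 - 0.95^k | Significant in favour of intervention, 1 - 0.975^k |
|---|---|---|
| 1 | 5% | 2.5% |
| 20 | 64.2% | 39.7% |
| 24 | 70.8% | 45.5% |

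A false claim of efficacy needs a result in favour of the intervention, so the last column is the relevant one.

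**4. Allow for shared data.** For each outcome, standardised treatment differences at baseline, 3 and 12 months were simulated under no effect (200,000 runs per setting). Level and change tests were built from the same draws. The assumed within-outcome correlation over time was 0.3 to 0.7. Results for 20 tests:

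| Assumed between-outcome correlation | Either direction | Favouring intervention |
|---|---|---|
| 0 | 55-58% | 32-35% |
| 0.3 | 52-55% | 28-30% |
| 0.5 | 47-50% | 24-27% |
| 0.7 | 39-42% | 20-22% |

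With 24 tests, the favourable-direction range is 22-40%.

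**5. Alcohol only.** If the alcohol score is tested as level and change at both visits (4 tests), the rate is about 15-16% in either direction and about 8% in favour. If only the single ANOVA interaction test counts, it is 5% two-sided.

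**6. Why levels and changes can disagree.** With baseline-to-follow-up correlation r and equal variances, the level and change statistics for one outcome and visit correlate at sqrt((1 - r)/2). For r = 0.3, 0.5 and 0.7 this gives 0.59, 0.50 and 0.39. These are far from 1, so the two tests often differ.

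**7. What the stated sample offers for alcohol.** The detectable standardised difference with 251 per group, two-sided 5% and 80% power is 2.80 x sqrt(2/251) = 0.25.

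**The case against.** The strongest reply is that the protocol does have an implicit order. The aim, the first hypothesis and the only outcome-specific model all point to alcohol, and the model yields one interaction test. On that reading the error rate is 5% and the other comparisons are supportive. This is a fair reading, but no section adopts it. It would also leave adherence, the only outcome for which the trial is powered, without a claim.

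A reader might infer more than the documents support in three ways:
- **That the outcomes are co-equal, each is tested at 5%, and any one can trigger the efficacy verdict.** None of this is written. The 5% level appears only in the sample size paragraph, and the Control arm section names no test, which is different from accepting every test.
- **That the chance of a false efficacy claim is 50-60%.** That figure counts significant results in either direction, including those favouring control, and holds only for low to moderate between-outcome correlation.
- **That the simulated percentages are precise.** All correlations are assumed, the count is 20 or 24, health status is not defined as one score, and the failure outcomes are binary and partly defined by change already. Only the order of magnitude is safe.

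Multiplicity ordering and baseline adjustment can also be set in an analysis plan that is not shown. That stands for the procedure. It does not remove the disagreement inside the protocol over which outcome the trial is designed to test.

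**Conclusion.** The point holds as a conflict within the protocol, and it should be corrected. The powered outcome differs from the outcome in the aim, the first hypothesis and the model. The same five outcomes are compared in two forms that can disagree, and the efficacy verdict that governs later treatment of controls is undefined.

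The size is conditional. If any of the 20 comparisons could count, a false claim of benefit has a chance of about 20-35% under the assumed correlations, with 40% as the figure for independence. That is at least eight times the 2.5% of a single test (20/2.5 = 8). If only the alcohol interaction test counts, there is no inflation. The protocol does not say which of these applies, and that is the defect.

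**What to change.** - **Name one primary outcome, visit and test.** AUDIT score at 12 months would match the aim and the first hypothesis. Make ART adherence the key secondary, tested only if the primary is significant, and label the rest exploratory.
- **Merge objectives 4 and 5** into one baseline-adjusted comparison per outcome and visit. This halves the list from 20 to 10 and removes conflicts between levels and changes. Baseline data are already collected.
- **Restate power.** Keep the adherence calculation for the key secondary, and add that 251 per group detects a standardised difference of about 0.25 on the alcohol score at 80% power. The sample need grow only if a smaller effect is expected.
- **Define efficacy by the primary test** wherever the protocol uses the term, including the Control arm section. Reconcile that section's condition with the unconditional statement under Ethical issues.

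The cost is protocol wording and a rewritten power statement, with no new data. The real downside is that adherence and the other outcomes could no longer carry an efficacy claim alone.

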#### Hypotheses:

- HIV positive patients who are medium risk drinkers in the intervention group decrease drinking more than those in the control group;
- The levels of alcohol consumption of patients in the intervention group will continuously reduce over a 12 month assessment period;
- In the intervention group, adherence levels to ART during follow up will be higher, alcohol consumption lower, quality of life and health status better and number of therapies failing virologically or immunologically will be lower compared to the control group at post intervention;

# Methodology

#### Design

The study design for this efficacy study is a randomized controlled trial with 3 and 12-month follow ups.

#### Study population and participants

The sample will include HIV positive out-patients at the primary care clinics in the area. HIV positive out-patients will be screened for alcohol problems, and those identified as medium risk drinkers will be randomized into an intervention or control group.

#### Inclusion criteria

-HIV 1 positive male and female patients

-Outpatients

-18 years and above

-No mental impairment

-Medium risk drinkers (i.e. 8-19 for men and 7-19 for women on the AUDIT questionnaire)

#### Exclusion criteria

-A score of 20 and above on the AUDIT questionnaire

-A score of less than 8 for men and less than 7 for women on the AUDIT questionnaire

-Pregnant patients

-Patients already under alcohol reduction treatment

-Patients with mental impairment

#### Sample size calculation

The sample size was calculated using Open Epi (available on www.openepi.com), for a two arm randomized controlled trial. With 80% power, a significance level of 5%, two sided-tests, assuming that adherence levels to ART overall are 90% in Africa. The adherence level of moderate alcohol users compared to abstainers and minimal alcoholusers shows an odds ratio of 0.480^27^. The minimum sample size for each group is 251 patients. To accommodate a drop-out rate of 10% overall, the sample size for each group will be 276, making a total of 552 patients.

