#### Procedure

The procedure follows the procedure of the main protocol.

Universal screening of all presenting HIV out-patients will be done. All consecutive HIV positive clients visiting the out-patient department will be screened for alcohol problems and randomized into an intervention or control group. Randomization will be done by a remote computer to generate numbers for intervention and control. Research assistant 1 will ask for consent from patients attending the hospital out-patient department to participate in the study, i.e. do a baseline assessment using the AUDIT questionnaire. Research assistant 1 will not be involved in delivering treatment. Research assistant 2 will score the results of the alcohol test section of the questionnaire. Clinic out-patients who score 8-19 for men and 7-19 for women on the AUDIT questionnaire after screening (risky drinkers) will be included in this study. Patients with a score of 20 and above on the AUDIT (with probable alcohol dependence) will be referred for further management. Additional information of the patients will be collected using the data collection instruments. Research assistant 2 will then check the random numbers which allocate the case to the intervention arm or control arms. Research assistant 2 will carry out the intervention for all the participants, after which they will be followed up at 3 and 12 months (which are standard visit intervals for the follow up of the HIV care), and assessments will be done by Research assistant 1, who will be blinded to the intervention allocation of the participants. In the event of a drop-out, at least six individual attempts will be made to contact patients by telephone and letter. Even if a contact was not successful at either follow up point, further attempts will be made at any next follow up point. Sampling will occur throughout all hours of clinic operation over a 3-month period. Two-hundred and seventy six patients will be recruited from hospital out-patient departments. Patients will be offered a drink (soda, water) during the interviews.

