#### Assessment of adherence to ART (Annex 5)

###### Visual Analog Scale (VAS)

The 30-day visual analog scale (VAS) provides an overall adherence assessment for a one-month period. The VAS has been validated in resource-limited settings^35,36^. Adherence levels assessed from the VAS are defined as follows: full adherence=100%, partial adherence: between ≥95% and <100%; and non-adherence as <95% of prescribed doses taken in the past 30 days. The VAS will be assessed at baseline for patients who are already on ART and on any follow up visit if the patient is on ART.

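### The stated 80% power is for ART adherence, but ART use is not required for entry and the 276 per group makes no allowance for patients without that outcome

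*Protocol*

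**What the plan says.** Sample size calculation sets the design parameters as follows: "With 80% power, a significance level of 5%, two sided-tests, assuming that adherence levels to ART overall are 90% in Africa". The effect comes from a cited meta-analysis: "The adherence level of moderate alcohol users compared to abstainers" and minimal users is reported there as an odds ratio of 0.480. This gives a minimum of 251 per group. The only inflation is for attrition: "To accommodate a drop-out rate of 10% overall, the sample size for each group will be 276", or 552 in total.

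The Inclusion criteria begin with "HIV 1 positive male and female patients" and add outpatient status, age, no mental impairment and a medium-risk AUDIT score. Neither they nor the Exclusion criteria mention ART. Procedure screens all consecutive HIV-positive attenders.

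Under Assessment of adherence to ART, "The VAS will be assessed at baseline for patients who are already on ART". The same sentence extends the measurement to any follow-up visit at which the patient is on ART. The pill count compares dispensed with remaining medication, so it too yields ART adherence only for someone who has been dispensed ART.

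Procedure also states: "Two-hundred and seventy six patients will be recruited from hospital out-patient departments". The sample size section, the time line and the budget all use 552.

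**The concern.** The sample size counts every enrolled patient towards a comparison that only some may be able to enter. The wording of the adherence section shows that the authors expected some participants not to be on ART, yet 276 covers drop-out and nothing else. A statistical analysis plan would not repair this, because the number, its basis and the eligible population are all fixed in the protocol and do not match.

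A null adherence result would be read as coming from a trial with 80% power when the true figure may be lower. The effect size adds to the risk of misreading: it is a difference between groups defined by how much they drink, used as though it were a difference between randomised arms.

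The recruitment sentence in Procedure is a separate defect in the same calculation. It is the operative instruction to the field team, and read literally it halves the trial.

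**Working it through.** **Inputs.** From Sample size calculation: reference adherence 90%, odds ratio 0.480, two-sided 5%, power 80%, equal groups, drop-out 10%. From the adherence section: the outcome exists only in patients on ART at the visit. The share on ART, *f*, is not given; I take 50% to 100% as an assumed range.

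**Second proportion.** Odds at 90% are 0.90/0.10 = 9. Then 9 × 0.48 = 4.32, and 4.32/5.32 = 0.812. The difference is 8.8 percentage points.

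**Reproducing 251.** With p̄ = (0.900 + 0.812)/2 = 0.856, the averaged-variance formula is

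n = 2 p̄(1 − p̄)(z₀.₉₇₅ + z₀.₈₀)² / d² = 0.2465 × (1.960 + 0.842)² / 0.0880² = 250.02, rounded up to 251.

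This matches the protocol. The pooled formula without continuity correction gives 249. Then 251 × 1.10 = 276.1, the stated 276. The arithmetic is sound for a population entirely on ART.

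**Power with an ART share.** The evaluable number per group is 276 × 0.90 × *f*, and

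z_power = [d√n − 1.960 √(2p̄(1 − p̄))] / √(p₁(1 − p₁) + p₂(1 − p₂)).

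For *f* = 100%, n = 248.4 and z = (0.0880 × 15.76 − 1.960 × 0.4965)/0.4926 = 0.839, which is 79.9% power. In the same way:

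| Share on ART at the visit (assumed) | Evaluable per group | Power |
|---|---|---|
| 100% | 248 | 79.9% |
| 90% | 224 | 75.6% |
| 80% | 199 | 70.6% |
| 70% | 174 | 64.8% |
| 60% | 149 | 58.1% |
| 50% | 124 | 50.6% |

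**Without drop-out.** If nobody were lost, a 90% ART share would leave 276 × 0.90 = 248 per group, again 79.9%. So about 90% on ART is needed even in the best case.

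**Under the protocol's imputation rule.** Data Analysis replaces data for patients lost at both follow-ups with baseline values. If all are on ART and all 276 per group are analysed, power is 83.9% if the full difference holds throughout. If the lost 10% of the intervention group show no benefit, that group's rate is 0.90 × 0.900 + 0.10 × 0.812 = 0.891. Power against 0.812 is then about 75%.

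**Recruiting 276 in total.** 276/2 × 0.90 = 124 per group evaluable, about 51% power with everyone on ART.

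**The case against.** Several points on the other side are fair.

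- A reader might infer that patients not on ART at entry add nothing to the adherence comparison. That goes too far. Someone who starts ART before a follow-up visit is measured there and counts in the comparison of levels at 3 and 12 months (objective 4). What such a patient lacks is a baseline value, for the comparison of changes (objective 5) and for baseline imputation.
- A reader might infer that power is in fact far below 80%. Nothing in the protocol fixes the ART share. At 90% the shortfall is modest; the low figures need shares that the document neither supports nor excludes.
- The figure of 248 evaluable per group sets aside the imputation rule. As shown above, that rule can move power either way, and it cannot supply an adherence value to someone who has no baseline one.
- It is tempting to call the odds ratio an upper bound, or to say that every intervention patient must change. The documents support neither. A net 8.8 patients per 100 would have to move from non-adherent to adherent, and the reference group includes minimal drinkers, so reduced drinking is a plausible route. What stands is that the ratio contrasts drinking groups and does not estimate what the intervention achieves.
- One could fault the drop-out inflation, since 251/0.90 = 279. Three patients per group, or 79.9% against 80%, is immaterial.
- The first hypothesis, "HIV positive patients who are medium risk drinkers in the intervention group decrease drinking more than those in the control group", might suggest that the AUDIT score must be named the main outcome. That is a design preference. Adherence is also among the objectives and hypotheses, and Data Analysis provides t-tests and chi-square tests for group differences.
- The 276 in Procedure is probably a slip for 276 per group, since 552 appears in three other places. It still needs correcting.

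**Conclusion.** The point holds in this form. The 80% power for adherence is conditional on essentially every participant being on ART at the assessed visit. The protocol does not state that condition, and its eligibility criteria do not secure it.

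The direction is certain under the stated inputs and 10% drop-out: there is no reserve, so any share below 100% falls short of the 79.9% obtained when all are on ART. The size is not certain. The range from 75.6% at 90% on ART to 50.6% at 50% rests on an assumed share, on the 90% against 81.2% difference, and on analysing only those with follow-up. The documents do not support a claim that power is actually at the low end.

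The 276 against 552 discrepancy is a plain inconsistency. Its consequence, about 51% power, arises only if the sentence in Procedure is followed literally.

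**What to change.** In Sample size calculation:

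1. Define the adherence comparison as being among patients on ART at the assessed visit. Say that patients who start ART after baseline enter the comparison of levels but not the comparison of changes.
2. State the expected share on ART, and the power or the detectable difference for the resulting evaluable number per group.
3. Say that the odds ratio of 0.480 compares moderate drinkers with abstainers and minimal users, and is a planning value that does not estimate the intervention's effect.

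In Procedure, change the recruitment target to 276 per group, 552 in total, to agree with the sample size section, the time line and the budget.

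The cost is a few sentences and a less favourable stated power for adherence. Enrolment beyond 552 is not needed.

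### The 80% power for ART adherence assumes that every patient retained has an adherence value, but being on ART is not an entry criterion and adherence is measured only in patients on ART

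*Protocol*

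**What the plan says.** The only sample-size calculation (Protocol, Sample size calculation) concerns adherence to ART. It is set up "With 80% power, a significance level of 5%, two sided-tests", "assuming that adherence levels to ART overall are 90% in Africa", and takes its effect from a meta-analysis: "The adherence level of moderate alcohol users compared to abstainers and minimal alcoholusers shows an odds ratio of 0.480". It concludes: "The minimum sample size for each group is 251 patients". After an allowance for 10% drop-out, "the sample size for each group will be 276, making a total of 552 patients".

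The Inclusion criteria ask for "HIV 1 positive male and female patients" who are adult out-patients in the medium-risk AUDIT range. Neither they nor the Exclusion criteria mention ART. The Procedure screens all consecutive HIV-positive out-patients.

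The adherence section expects some participants to be off treatment: "The VAS will be assessed at baseline for patients who are already on ART", and at later visits only if the patient is then on ART. The pill-count formula divides pills dispensed minus pills returned by pills expected to be taken, so it too exists only for patients with dispensed ART.

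**The concern.** A patient with no ART prescription has no adherence value, so such patients cannot count towards the 251. The step from 251 to 276 allows for drop-out and for nothing else. The power statement therefore describes a comparison in which every retained patient is on ART, while the protocol's own measurement rules say that some may not be.

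Two things are at stake. A null adherence result would be read as coming from an 80%-powered comparison when the real figure could be well below that. Change in adherence (Objective 5b) also cannot be computed for anyone off ART at baseline, and the protocol does not say which patients that comparison covers.

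**Working it through.** **Inputs.** From Sample size calculation: reference adherence p1 = 0.90, odds ratio 0.480, two-sided 5%, power 80%, 276 per group, 10% drop-out. The share s of patients on ART at the time of measurement is not in the protocol. It is an assumption here, shown from 100% down to 50%.

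**Step 1: the second proportion.** Odds at 0.90 are 9; 9 × 0.480 = 4.32; p2 = 4.32 / 5.32 = 0.812. The difference is d = 0.0880 and the mean proportion is p̄ = 0.856.

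**Step 2: reproduce 251.**
- Simple pooled formula: (1.960 + 0.8416)² × 2p̄(1 − p̄) / d² = 7.849 × 0.2465 / 0.00774 = 250.02, which rounds up to 251.
- Formula with pooled variance under the null and separate variances under the alternative: 248.8, so 249.

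The stated 251 is sound for its inputs. It is the number per group with an adherence value.

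**Step 3: patients left after the planned loss.** 276 × 0.90 = 248.4 per group if everyone is on ART. The plan therefore has no spare patients to cover those off ART.

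**Step 4: power with m evaluable patients per group.**

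Power = Φ{[d√m − 1.960 √(2p̄(1 − p̄))] / √(p1(1 − p1) + p2(1 − p2))}

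The two square roots are √0.2465 and √0.2426. Example at s = 80%: m = 276 × 0.90 × 0.80 = 198.7; d√m = 1.240; (1.240 − 0.973) / 0.4926 = 0.542; Φ(0.542) = 70.6%.

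**Step 5: a second count.** The Data Analysis section fills in one missing follow-up from the other, and replaces complete loss with the baseline value. If that rule is applied to adherence, drop-outs who were on ART at baseline stay in the analysis and the nominal count becomes 276 × s. The power in the last column is the same formula at that count. It takes no account of dilution of the effect by carried-forward baseline values.

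| Share on ART (assumed) | Evaluable per group, 276 × 0.9 × s | Power | Nominal count with imputation, 276 × s | Nominal power |
|---|---|---|---|---|
| 100% | 248 | 79.9% | 276 | 83.9% |
| 95% | 236 | 77.9% | 262 | 82.0% |
| 90% | 224 | 75.6% | 248 | 79.9% |
| 80% | 199 | 70.6% | 221 | 75.1% |
| 70% | 174 | 64.8% | 193 | 69.4% |
| 60% | 149 | 58.1% | 166 | 62.7% |
| 50% | 124 | 50.6% | 138 | 54.9% |

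Even on the more generous count, 251 per group needs 251 / 276 = 91% on ART. Imputation cannot supply a value for a patient off ART throughout, who has nothing to carry.

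**The case against.** **The size of the loss is unknown.** The protocol gives no share on ART. If nearly all out-patients at these clinics are treated, the shortfall is trivial: 79.9% at full coverage and 77.9% at 95%. This stands. A reader might infer that 80% power is definitely not delivered, or that the trial is badly underpowered. The documents do not support that. They show only that the figure is not assured.

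**Baseline status is not the whole story.** Levels of adherence are compared at 3 and 12 months (Objective 4b), and the VAS is taken at any follow-up visit when the patient is on ART. Patients who start treatment after baseline become evaluable, so the share that matters for levels is the one at follow-up. This also stands. It rules out the tempting reading that 251 is the number needed on ART at randomisation. With 251 on ART at randomisation, a 10% loss leaves 226 and 76% power.

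**Adherence is not named as primary.** The aim, the first two hypotheses and the one named longitudinal model (on the alcohol use score) concern drinking, and AUDIT is collected at every study visit whatever the patient's ART status. The alcohol comparison is thus unaffected. But adherence is the only outcome for which the protocol claims any power, so the claim still has to match who will be measured.

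**Imputation keeps drop-outs in.** This softens the figures, as the last two table columns show, but only nominally, because carried-forward baseline values pull the groups together.

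**Conclusion.** The point holds as a mismatch between the sample-size statement and the measured population. The calculation of 251 is correct for its inputs, but it is applied to all enrolled patients less drop-out, while the protocol admits patients who will have no adherence value. With the planned 10% loss, power for adherence falls below 80% unless essentially all patients are on ART. It would be 75.6% at 90% on ART, 70.6% at 80% and 50.6% at 50%.

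These figures rest on the protocol's own 90% and odds ratio of 0.480, on equal shares on ART in both groups, and on a share on ART that is assumed. The conclusion is confined to adherence, and does not extend to the alcohol-score comparison.

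**What to change.** In Sample size calculation:
- state that 251 per group is the number with an evaluable adherence value at follow-up;
- give the expected share on ART and its source;
- restate the adherence power that 552 enrolled deliver at that share.

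State the comparison sets as well. Analyse change in adherence (Objective 5b) in patients on ART at randomisation. Levels at 3 and 12 months may also include patients who start ART later, but starting ART happens after allocation, so the set on ART at randomisation should be kept as the comparison protected by randomisation.

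Stratifying the allocation list by baseline ART status is optional. It would balance that set but would not repair the power figure. ART status would have to be read from the start date and drug tick-boxes in Annex 4, which has no yes/no item.

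The change costs protocol wording and a less favourable power statement. It needs no extra patients, but it discloses the shortfall without removing it. If the sponsor wants to keep 80%, enrolment per group is 251 / (0.9 × share): for example 251 / 0.72 = 349 per group, 698 in total, at 80% on ART.
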